### Qualitative Component

We will conduct interviews with approximately 12 participants of the AIM intervention group. This sample size is sufficient when using a qualitative descriptive approach to generate rich, detailed descriptions and meaningful data [49,50]. In these interviews, we will use maximum variation sampling to include women who have specific characteristics (eg, francophone, new immigrant, and rural) and ask them about their perceptions of the program and their recommendations for further program development. We will also invite any intervention group participants who did not complete the AIM program to participate in an interview to learn about their experiences in the program and ask for any recommendations they may have to help improve the program. All facilitators who deliver the AIM intervention to trial participants will be invited by telephone or email by the research coordinator to complete a qualitative interview. While all will be invited, we hope that at least 4 to 5 will volunteer to participate in the interview.

At the 9-month follow-up data collection point, the research coordinator will invite women from the AIM intervention group to take part in a virtual interview. To be eligible to be invited for the interview, participants must have completed the empowerment component and at least 10 out of 12 social support sessions. In these interviews, the research coordinator will try to recruit a diverse sample of women who represent the characteristics of the participants and ask them about their perceptions of the program and their recommendations for further refinement of the program to meet the needs of diverse midlife and older women. The informed consent form will be shared by email or by postal mail.

The research team will also conduct an exploratory qualitative analysis on the data recorded by the program facilitators. Facilitators will be instructed to record the date and length of each session and take notes. The notes will detail the topics discussed with participants, the support and resources offered to participants, and any questions or concerns raised by the participants. The analysis of this exploratory data will summarize what topics are discussed and what supports are provided to participants.

All qualitative data will be analyzed using thematic analysis [51]. This is a form of pattern recognition allowed for inductive coding [52] and is particularly useful in understanding the influences and motivations related to how people respond to events [53]. The data coding process will involve generating initial codes, searching for themes, reviewing themes, and defining and naming themes that result in thematic codes representing patterned responses within the dataset [51]. Qualitative interview data from the participants of the intervention group will provide important insights about further refinement of the program to meet the needs of diverse women. Qualitative interview data from facilitators will provide important insights about the training program they participated in, delivery methods and content of the program to consider in further development, and scale-up and spread of the program.

### Ethical Considerations

#### Overview

This trial required research ethics approval from the institutions where the investigators are located, which included Dalhousie University, the University of New Brunswick, St. Francis Xavier University, the University of Prince Edward Island, and the Université de Moncton (Table 3). To facilitate this process, the application was first submitted and approved by Dalhousie University’s Social Sciences and Humanities Research Ethics Board and then subsequently submitted to the other research ethics boards. The trial was deemed more than minimal risk and, therefore, underwent a full, rigorous review at 4 of the 5 institutions. St. Francis Xavier University conducted an expedited review because the trial was previously approved by Dalhousie University.

**Table 3 table3:** Institutional review board approvals.

Institutional ethics review board	Date of approval	REB^a^ file number
Dalhousie University Health Sciences Research Ethics Board	July 11, 2023	2023-6548
St. Francis Xavier University Research Ethics Board	August 23, 2023	26598
Université de Moncton Ethics Committee for Research Involving Human Beings	September 6, 2023	2324-005
University of New Brunswick Research Ethics Board	September 23, 2023	2023-110
University of Prince Edward Island Research Ethics Board	October 6, 2023	6012156

^a^REB: research ethics board.

#### Informed Consent Process

All potential participants will be provided with information about the study and will receive either an electronic or a mailed copy of the informed consent form and will be given an opportunity to review it and ask questions before deciding whether they wish to volunteer to participate. The consent form will be reviewed verbally with the potential participant, and verbal consent will be obtained before beginning data collection. The person collecting the data will electronically record that consent was obtained before the first data collection point and before the 2 follow-up data collection points. After consenting to take part in the study, the participants and research staff will agree on a time to conduct the baseline interview by telephone or video call. At the beginning of each follow-up interview, key components of the consent form will be reviewed, and any questions raised will be responded to before the interview proceeding.

Participants can choose to withdraw by canceling the scheduled data collection session, withdrawing at the beginning of the session, or withdrawing after the data collection session begins. Participants can withdraw their data up to 7 days after a data collection session. This information is included in the consent form, and this will be emphasized during the review of the consent form before data collection begins.

#### Confidentiality and Anonymity

All study data will be kept confidential, and the participants’ identity (eg, names and identifying information) will not be made known in any reports of the results. A participant ID number will be used for any quotes in reporting qualitative results. Qualitative interviews will be recorded on the research coordinator’s secure laptop. The transcription function in Microsoft Word will be used to create a draft transcript that will then be edited by the research team members. Once a transcript is checked and edited by a research team member, the interview transcripts and the quantitative data will be shared among the team members using OneDrive, a secure, password-protected file-sharing system hosted by Dalhousie University. No hard copies of any study documents that could identify a participant will be retained.

The digital recordings will be kept only until the transcript is prepared, and then, the recording will be destroyed. Qualitative data, numerical key codes, and contact information of the participants will be retained by the co–principal investigators on a password-protected computer and on the OneDrive systems at Dalhousie University and the University of New Brunswick. These data will be destroyed 5 years after the publication of study results. Each participant will be given the option of allowing the co-principal investigators to retain the deidentified quantitative data indefinitely to be used in potential future research studies or for teaching purposes (eg, in a course with content on family violence). Providing this consent is not required for inclusion in the study.

This study focuses on midlife and older women who are currently experiencing IPV and are either living with an abusive partner or are in the process of leaving an abusive partner. There are different laws regarding the duty to report elder abuse in different provinces where we will be collecting data, and we will follow the procedure in each province. However, the issues about when to report typically are focused on the situations in which people do not have the physical or mental capacity to protect themselves or make their own decisions. If in the process of conducting data collection, the abuse of a child or an adult in need of protection is disclosed, the facilitator will contact the appropriate child protection or adult protection services in the location where the data are being collected.

The participants could be clients of an agency the facilitators work for. The participants will be assured that whether they choose to participate in the AIM study or not, there will be no negative repercussions on other services they access.

#### Compensation

All participants in the quantitative study will be provided with an honorarium of CAD $125 after completion of their baseline surveys. The honorarium is provided for agreeing to take part in the study and is not provided as an incentive. An additional CAD $20 honorarium will be provided to those who participate in a qualitative interview. All facilitators will receive an honorarium of CAD $45 if they participate in a qualitative interview. All participants will be given the option of receiving a physical gift card sent in the mail or a digital gift card sent via email.

#### Potential Harms to Participants

For participants living at home with the perpetrator, the participant may be at risk if the perpetrator finds out they are participating in the study. We will ensure personal safety of the participants in various ways at each stage of the research, including participant recruitment. The participants are welcome to participate virtually at a time and location that is chosen by them. If they need to end participation at any time, they are welcome to do so, and the facilitator will follow up at a time that is suitable and safe for them. As both the empowerment and social support components are delivered individually to participants, we can be very flexible about when the intervention is delivered.

The facilitators will teach the participants about ensuring digital security (eg, clearing browser history) during the empowerment component of the intervention. The participants will also be provided with information about local resources and services that are available. If the participant is in immediate danger during the time the facilitator is talking with them, they will instruct the participant to call 911, and if that is not possible, they will call 911 on the participant’s behalf.

#### Data Monitoring

This pragmatic RCT does not have a data monitoring committee. Participant safety will be monitored through the research coordinator’s regular communications (eg, biweekly communication when the facilitators are delivering the intervention) about any potential harm to the participants. However, we do not expect that the intervention will cause harm to the participants. The main potential risk that we identified is for the participants currently experiencing abuse and potentially living at home with the perpetrator. The perpetrator may find out about the study and may be against participation. The participants can leave the study at any time, and they have been provided with information about local resources and services that are available.

### Access to Data

The data from this trial will not be publicly available due to the risk of compromising the privacy of the research participants.

### Dissemination of Results

The findings of this study will be disseminated in several ways. We will submit a journal article to a peer-reviewed journal (eg, *Journal of Women and Aging* and *Violence Against Women*). We will ensure that the article is open access to ensure accessibility. We will deliver conference presentations at academic and professional conferences (eg, Canadian Association on Gerontology Annual Conference and Canadian Domestic Violence Conference). The intended audience will be researchers, practitioners, students, trainees, and policy makers. We will also develop and disseminate other research outputs that are required by the funders (eg, plain language summary, brief video, and infographic) in English and French. These accessible documents will be important for all our team members to share with their networks.

If the AIM intervention is determined to be effective, we will use the feedback we receive from the qualitative interviews with staff and participants to refine the staff training program and make it publicly available in both French and English. The final program materials will be distributed to service providers who work with victims of IPV and elder abuse in the Maritime provinces. In addition, the final program will be made freely available to anyone interested in supporting midlife and older women experiencing IPV and will be posted and publicized in the resources section of the Muriel McQueen Fergusson Centre for Family Violence Research website. The program will also be posted and distributed through the resource hub of the Canadian Network for the Prevention of Elder Abuse.

## Results

The funding from the Public Health Agency of Canada for this study began in January 2023. From January to June 2023, the initial ethics proposal was drafted and research staff were hired. Research ethics applications were submitted to each university from July to October 2023. Table 2 provides the research ethics board approval numbers for each institution. Recruitment of facilitators began in July 2023 and continued till May 2024. The principal researcher conducted 5 AIM training sessions with 12 facilitators from the Maritime provinces. Four of the training sessions were conducted in English only, and 1 training session was provided to a francophone facilitator via Zoom using simultaneous translators. Participant recruitment and data collection will be carried out from November 2023 to January 2025. Data analysis will continue throughout the data collection period, and results will be disseminated by December 2025.

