**Results:**

A total of 12 facilitators have been trained to deliver the AIM intervention to trial participants. Participant recruitment and data collection will be completed in January 2025. Data analysis will continue throughout the data collection period, and the results will be disseminated by December 2025.

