#### Components of AIM

The empowerment component is derived from the empowerment model by Dutton [37] to increase women’s safety. This component will involve the facilitator providing a 1-hour-long individual one-on-one information-sharing session with the participants that will be delivered virtually by telephone or video call. These sessions will include providing information on recognizing increased danger and how to use an individualized safety plan adapted for older women, providing information about cycles of violence, providing community and legal resources, and developing goals and strategies for the future. In addition to discussing this information, print materials will be provided electronically (via email) or in hard copy (via postal mail). Thus, this component clearly contributes to awareness raising and also empowers the women to develop changes in the future.

The social support component is based on the social support theory by Cohen [38] that involves tangible and perceived social support to contribute to health and well-being. This component will involve the facilitator scheduling weekly telephone or video calls over a course of 12 weeks at a time that is convenient to the participant. The duration of calls is variable and would average approximately 20 minutes per call. The calls are intended to provide encouragement and support and to answer questions the participant may have about using or applying the resources provided in the empowerment component. There are no specific or scheduled topics that are planned for each session. These are very individualized and based on the women’s needs and questions that each woman may wish to discuss. For example, facilitators will be prepared to help women with recognizing their past abuse and processing the abuse as well as providing support to women who are undergoing court proceedings and legal issues. The social support provided through the weekly contact is a key component of the intervention in addition to the topics discussed.

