### Sample Size

For the quantitative portion of the study (ie, the RCT), we determined an appropriate sample size that would be sufficient to contribute to the evidence base. We reviewed the sample sizes analyzed in the systematic review we conducted, the sample sizes of the studies focused on women experiencing IPV in midlife and older, and the sample size calculations in the study from which we have adapted the program [34]. We used our prior experience in recruiting midlife and older women as well as the resources available to conduct this research. We then concluded that recruiting 30 participants per arm is sufficient, that is, 30 women randomized into the intervention arm and 30 women randomized into the control arm. To account for a 15% attrition rate identified in a similar study [39], we will recruit 70 women, with 35 randomized to each group.

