### Participant Involvement by Group

Participant recruitment began in October 2023 and is expected to continue until July 2024. Participants will complete the screening and informed consent process with research staff and will be randomized upon completion of their baseline surveys. Participants that have been randomized to the intervention group will be matched with a facilitator in their region. The facilitators will follow up after randomization and schedule the 1-hour-long information-sharing session (ie, empowerment component) and then continue to follow up with the weekly calls for 12 weeks (ie, social support component). Quantitative survey data will be collected from all the participants at 3- and 9-month follow-ups. Follow-ups with participants in the AIM intervention group will take place 3 and 9 months after their final social support session. For participants randomized to the comparison group, follow-ups will take place 3 and 9 months after they have completed the baseline surveys. We estimate the total time commitment for participants to be 11 hours for those randomized to the AIM intervention group and 4 hours for those in the comparison group. Table 2 breaks down the estimated time commitment for each study activity.

**Table 2 table2:** Participant involvement by group.

Study activity	Time commitment for participants in the AIM^a^ intervention group (hours)	Time commitment for participants in the comparison group (hours)
Informed consent process	0.5	0.5
Baseline data collection	1.5	1.5
Empowerment component	1	—^b^
Social support component	6	—
3-month follow-up	1	1
9-month follow-up	1	1
Total time commitment	11	4

^a^AIM: advocacy intervention for midlife and older women.

^b^Did not participate.

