### Statistical Analysis

Quantitative data will be exported from REDCap as a spreadsheet and then uploaded into SPSS (IBM Corp) for quantitative analysis. Participants in the AIM intervention group need to complete the empowerment component and attend at least 10 out of 12 weekly calls of the social support component for their quantitative data to be included in the analysis.

Descriptive statistics will provide a profile of study participants, including demographics for the whole sample and for those in each of the 2 groups. The provisional effect of the intervention will be tested using a prospective chi-square test of independence between the 2 groups for categorical data (Fisher exact test) at 3 and 9 months. Repeated measures analysis of variance will measure mean differences between the groups on continuous variables at 3 and 9 months.

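### Recruitment to July 2024, follow-up to 9 months and a January 2025 close of data collection cannot all hold; enforcing the close would lose 9-month data unequally between arms

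*Protocol article*

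**What the plan says.** Four statements in the protocol article bear on the calendar.

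- **Recruitment window** (Participant Involvement by Group): "Participant recruitment began in October 2023 and is expected to continue until July 2024".
- **Follow-up clock** (same section). Intervention arm: "Follow-ups with participants in the AIM intervention group will take place 3 and 9 months after their final social support session". Comparison arm: "For participants randomized to the comparison group, follow-ups will take place 3 and 9 months after they have completed the baseline surveys". The length of the intervention is given under Components of AIM: "This component will involve the facilitator scheduling weekly telephone or video calls over a course of 12 weeks".
- **End of data collection**. The Abstract (Results) has: "Participant recruitment and data collection will be completed in January 2025". The main Results section has: "Participant recruitment and data collection will be carried out from November 2023 to January 2025".
- **Use of the 9-month data** (Statistical Analysis): "Repeated measures analysis of variance will measure mean differences between the groups on continuous variables at 3 and 9 months". Table 1 under Outcomes Measured schedules every outcome scale at 9 months.

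The sample size section allows for loss to follow-up as follows: "To account for a 15% attrition rate identified in a similar study [39], we will recruit 70 women, with 35 randomized to each group". The article nowhere describes a shorter follow-up for late entrants or a common administrative cut-off.

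**The concern.** Six months separate the end of July 2024 from the end of January 2025. A 9-month visit does not fit into that interval for a woman enrolled late, in either arm. It fits least in the intervention arm, where the 9 months begin only after the 12 weeks of calls.

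The 9-month assessment is one of the two post-baseline time points in the planned comparison. The qualitative interviews with intervention women are also arranged at that visit. If the close were applied as written, whether a woman has 9-month data would depend on her enrolment date and on her arm. Loss that differs by arm by construction is a threat to the comparison as well as a loss of numbers. An attrition rate borrowed from another study does not anticipate it.

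**Working it through.** **Inputs.** Recruitment starts in October 2023 (Participant Involvement by Group) or November 2023 (Results) and ends in July 2024. Data collection ends in January 2025, read as 31 January, the most generous day. Comparison visit = enrolment + 9 months. Intervention visit = enrolment + 84 days (12 weeks) + 9 months. The 84 days assume that calls start promptly after randomisation; any delay moves the visit later.

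**Step 1: does the stated end date reproduce?** Take the last enrolments.

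| Enrolled | Comparison, 9 months | Intervention, end of calls | Intervention, 3 months | Intervention, 9 months |
|---|---|---|---|---|
| 1 July 2024 | 1 April 2025 | 23 September 2024 | 23 December 2024 | 23 June 2025 |
| 31 July 2024 | 30 April 2025 | 23 October 2024 | 23 January 2025 | 23 July 2025 |

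It does not. January 2025 accommodates the last 3-month visit but no 9-month visit for a July enrolment. Counting only the 77 days from the first to the twelfth weekly call moves the intervention dates one week earlier, to 16 June and 16 July 2025, and changes nothing. Nor are the different clocks the sole cause: with both arms timed from baseline, women enrolled in May to July 2024 would be due in February to April 2025.

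**Step 2: latest enrolment that still allows a 9-month visit by 31 January 2025.**

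- Comparison: 31 January 2025 − 9 months = 30 April 2024.
- Intervention: 30 April 2024 − 84 days = 6 February 2024.

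Between 7 February and 30 April 2024, a comparison woman can supply 9-month data and an intervention woman enrolled on the same day cannot. Steps 1 and 2 need no assumption about the pace of recruitment.

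**Step 3: illustrative size, assuming even accrual to 31 July 2024.** Share reachable = days from the start to the cut-off ÷ days in the window.

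| Start | Intervention | Comparison |
|---|---|---|
| 1 October 2023 (305 days) | 129/305 = 42%, about 15 of 35 | 213/305 = 70%, about 24 of 35 |
| 1 November 2023 (274 days) | 98/274 = 36%, 12 to 13 of 35 | 182/274 = 66%, about 23 of 35 |

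These are before ordinary dropout. The plan's own allowance leaves 35 × 0.85 = 29.75, about 30 per arm. Still with even accrual, the first or last day of July 2024 and of January 2025, and lags of 77, 84 or 91 days, give 23% to 50% for intervention and 56% to 78% for comparison.

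**Step 4: how far the size depends on the accrual pattern.** Let x be the fraction of the October window elapsed at each cut-off, 0.423 and 0.698. If enrolment density falls linearly to zero, the share is 1 − (1 − x)²: 67% intervention and 91% comparison. If it rises linearly from zero, the share is x²: 18% and 49%. The direction of the gap is the same in each case; its size is not fixed by the documents.

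**The case against.** The best reply is that this is a wrong date, not a plan to truncate follow-up. Participant Involvement by Group says that surveys are collected from all participants at both follow-ups. January 2025 appears only in the status paragraph under Results and its echo in the Abstract, and July 2024 is only an expectation. That stands: the documents support a mistaken calendar date at least as well as a shortened trial, so the data loss is conditional on the close being enforced.

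Three stronger readings are tempting, and the documents do not support them.

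- *The trial cannot deliver a 9-month outcome.* Women enrolled early enough can supply one. What is impossible is a 9-month visit for every randomised woman by January 2025.
- *Most intervention women would have no 9-month data.* That follows under even accrual. Under the front-loaded pattern in step 4, about two thirds of intervention women would be reachable, and comparison women would stay above 30 (0.91 × 35 = 31.8) before dropout. The article reports that facilitators were still being recruited until May 2024, which makes strong front-loading less plausible but does not establish a curve.
- *Power at 9 months falls by a known amount.* The Sample Size section states no alpha, power, effect size or SD, so any such figure would rest on an effect chosen by the reader.

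Reading January 2025 as the end of recruitment does not rescue the dates. Both statements tie data collection to the same month, and even accrual from November 2023 to January 2025 would lower the reachable shares to 21% and 40%. The October versus November 2023 start is a small discrepancy and carries no weight of its own.

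**Conclusion.** The inconsistency is established by calendar arithmetic on the article's own dates. With enrolment in July 2024, the last 9-month visits fall in April 2025 (comparison) and about late June to late July 2025 (intervention), so the stated close is about three and six months too early respectively. The 3-month assessment is not materially affected if the close is the end of January.

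The consequence is conditional. If January 2025 is enforced, 9-month data stop at enrolment dates of 30 April 2024 (comparison) and about 6 February 2024 (intervention). This is an arm-dependent loss on top of the 15% allowed for attrition. The shares of 36-42% and 66-70% illustrate its possible scale and rest on assumed even accrual; they are not a forecast. Because the loss would fall unequally on the two arms at one of the two planned comparison times, this is more than a clerical slip.

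**What to change.** Reconcile the Abstract (Results), Participant Involvement by Group and Results sections:

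- Define the end of data collection as the date of the last scheduled 9-month visit in either arm under the stated follow-up schedule, about the end of July 2025 for enrolment through July 2024.
- State that all randomised women are followed to 9 months.
- Give one recruitment start and one recruitment end.

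This needs no additional participants and still precedes the December 2025 dissemination date. The price is about six more months of interviews that are already planned, and less time for the final analysis. Whether staff funding covers those months cannot be told from the article, which gives only the start of funding.

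If the close cannot move, the article should say that 9-month follow-up is incomplete by design and that the loss differs by arm. Bringing the last enrolment forward is not a practical alternative: the text reports facilitator recruitment up to May 2024 as past, so both cut-off dates had already gone by. Making 3 months the primary time point would change the design in order to repair a date.
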